**Secondary outcomes**	
SAE excl. mortality within 6 months after aSAH	Count
Health-related quality of life (EQ-5D-5L) at 6 months with the primary assessment being self- assessment of own health (EQ VAS; 0 to 100 point scale)	Continuous
Mean Fatigue Severity Scale (FSS) score at 6 months (1–7 levels)	Continuous
**Exploratory outcomes**	
Functional outcome according to modified Rankin Scale (mRS) at 6 months (1–6 scale)	Ordinal
The remaining dimensions of EQ-5D-5L (mobility, self-care, usual activities, pain/discomfort, and anxiety/depression) at 6 months (1–5 levels)	Count
Glasgow Outcome Scale Extended (GOSE) at 6 months (1–8 scale)	Ordinal
Reason for failure of EVD cessation (ICP elevation, drop in GCS by 2 points or more, and/or clinical deterioration)	Count
GCS on discharge from the Neuro Intensive Care Unit and Neurosurgical department	Count
Length of stay in Neuro Intensive Care Unit	Count
Length of stay in hospital	Count

*aSAH* aneurysmal subarachnoid haemorrhage, *EVD* external ventricular drain, *GCS* Glasgow Coma Scale, *ICP* intracranial pressure, *SAE* serious adverse events, *VP-shunt* ventriculoperitoneal-shunt

Secondary outcomes are:

Number of serious adverse events (SAE) not including mortality and defined according to International Conference of Harmonization of Good Clinical Practice (ICH-GCP) within 6 months (count outcome)Health-related quality of life (EQ-5D-5L) at 6 months [11] with the primary assessment being self- assessment of own health (EQ VAS; 0 to 100 point scale) (continuous outcome)Fatigue Severity Scale (FSS) mean score at 6 months [12]

Exploratory outcomes are:

Functional outcome according to modified Rankin scale (mRS) at 6 months [13, 14] (1–6 scale) (ordinal outcome)The remaining dimensions of EQ-5D-5L (mobility, self-care, usual activities, pain/discomfort, and anxiety/depression) at 6 months [11] (1–5 levels) (count outcome)Glasgow Outcome Scale Extended (GOSE) at 6 months [15] (1–8 scale) (ordinal outcome)Reason for failure of EVD cessation (ICP elevation, drop in GCS by 2 points or more, and/or clinical deterioration)GCS on discharge from the Neuro Intensive Care Unit and Neurosurgical departmentLength of stay in Neuro Intensive Care UnitLength of stay in hospitalEach component of the primary outcome will be analysed as exploratory outcomesEach component of the composite outcome will be analysed as exploratory outcomes

VP-shunt implantation is the consequence of failed EVD discontinuation and as such is included in the composite endpoint. The explanatory outcomes cover among other the reasons for the EVD discontinuation to be deemed a failure, e.g. intracranial hypertension or clinical deterioration.

### Sample size and power justification

#### Sample size estimation

Data from the only previous randomised clinical trial suggest a VP-shunt implantation proportion of 63% in patients with acute need of CSF diversion following aSAH [5]. The mortality following aSAH is commonly quoted to be 27% to 50%, while 5.8% of patients develop an EVD-related infection [2, 7]. Assuming an incidence of either of the three components of the composite primary outcome (VP-shunt implantation, all-cause mortality, or EVD-related infection) within 6 months of 80%, an *α* = 0.05 (two-sided), and a *β* = 0.20, 2 × 122 participants are required to detect a 20% relative risk reduction or increase calculated using R (R Core Team, Vienna, Austria)*.* For composite outcomes, one missing component will result in missingness in the composite outcome. Number and percent missing due to a missing component will be stated in the report or in a diagram to avoid biased result, e.g. from death alone.

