**Methods:**

DRAIN (*Danish RAndomised Trial of External Ventricular Drainage Cessation IN Aneurysmal Subarachnoid Haemorrhage*) is an international multicentre randomised clinical trial comparing prompt closure versus gradual weaning of the EVD after aSAH. The primary outcome is a composite of VP-shunt implantation, all-cause mortality, or EVD-related infection. Secondary outcomes are serious adverse events excluding mortality and health-related quality of life (EQ-5D-5L). Exploratory outcomes are modified Rankin Scale, Fatigue Severity Scale, Glasgow Outcome Scale Extended, and length of stay in the neurointensive care unit and hospital. Outcome assessment will be performed 6 months after ictus. Based on the sample size calculation (event proportion 80% in the gradual weaning group, relative risk reduction 20%, alpha 5%, power 80%), 122 participants are required in each intervention group. Outcome assessment for the primary outcome, statistical analyses, and conclusion drawing will be blinded. Two independent statistical analyses and reports will be tracked using a version control system, and both will be published. Based on the final statistical report, the blinded steering group will formulate two abstracts.

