### Outcomes

The primary outcome is a composite outcome of VP-shunt implantation, all-cause mortality, or EVD-related infection within 6 months after ictus. EVD-related infection is defined as a positive CSF culture, the use of intrathecal or systemic antibiotics for EVD-related infection, or both  (Table 1).

**Table 1 Tab1:** Outcomes of the DRAIN clinical trial

Outcomes	Type of data

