### General analysis principles

Statistical analyses will be handled using the latest stable version of R (R Core Team, Vienna, Austria) and/or Stata (StataCop LLC, Texas, USA). The analyses will be carried out using the intention-to-treat principle where all randomised participants will be included in all analyses. The baseline characteristics will be presented for each group (Tables 2 and 3). The threshold for significance for all outcomes will be below 0.05, as the primary conclusions will be drawn based on the primary outcome [22]. All the remaining secondary and exploratory outcomes will be interpreted as hypothesis generating outcomes.

**Table 2 Tab2:** Baseline characteristics based on simulated data

	A	B
*n*	122	122
Age (mean (SD))	57.8 (0.90)	59.1 (0.50)
Gender, female (*n*, %)	85 (70.9)	90 (73.8)
Hypertension (*n*, %)	46 (37.2)	51 (41.3)
Aneurysm location (*n*, %)		
ICA	19 (15.6)	14 (11.5)
ACA/ACOM	50 (41)	56 (45.9)
MCA	16 (13.2)	11 (9.1)
Basilar artery	25 (20.5)	23 (18.9)
Vertebral artery/PICA	8 (6.3)	10 (8.2)
Pericallosa	4 (3.2)	2 (1.6)
Treatment modality		
Endovascular	50 (41)	56 (45.9)
Surgical	72 (59)	66 (54.1)
WFNS grade		
I	60 (49,2)	55 (45,1)
II	11 (9,0)	12 (9,8)
III	7 (5,7)	12 (9,8)
IV	29 (23,8)	24 (19,7)
V	15 (12,3)	19 (15,6)
Hunt Hess		
1–3	70 (57.4)	74 (60.6)
4–5	52 (42.6)	48 (39.4)
Glasgow Coma Score on admission		
15–14	42 (34.2)	46 (37.7)
13–9	21 (17.1)	17 (14.1)
8–3	58 (47.7)	55 (45.1)
Modified Fisher		
0–3	52 (42.8)	56 (45.9)
4	70 (57.2)	66 (54.1)
Modified LeRoux		
0–5	50 (41)	56 (45.9)
6–16	72 (59)	66 (54.1)
Nicotine use		
Current	21 (17.1)	18 (14.6)
Former	13 (10.4)	10 (8.2)
Never	88 (72.1)	94 (77.1)
Intubated at admission (*n*, %)	45 (36.9)	41 (33.6)
Acute hydrocephalus (*n*, %)	78 (63.9)	71 (59.1)

**Table 3 Tab3:** Summarised results of outcomes based on simulated data

	A	B	Estimate	*p*-value
*n*	122	122		
Primary outcome				
Composite outcome—*n* (%)	43 (35)	36 (30)	*RR (95%CI)* 1.01 (0.99 to 1.03)	0.05
Secondary outcomes				
SAE excl. mortality—median (IQR)	340	320	*median diff (95%CI)* 330 (329 to 349)	0.45
EQ-5D-5L -	60	56	*mean diff (95%CI)* 58 (55.1 to 59.2)	0.69
Fatigue Severity Scale	4.3	4.8	*mean diff (95%CI)* 4.5 (3.9 to 5.3)	0.05
Mean FSS (SD)	5.21 (1.8)	4.1 (1,4)	*mean diff (95%CI)* 4.6 (-4 to 14)	0.69
Clinical fatigue (FSS ≥ 4)	88 (72.3)	82 (67.2)	*mean diff (95%CI)* 3.4 (3.29 to 4.21)	0.34
Components of the primary outcome				

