#### Handling of missing data

We will use an electronic case report form (eCRF) with a pragmatic design and incentive strategies to maximise complete registration to minimise the occurrence of missing data. If less than 5% of the data are missing on any primary or secondary outcome, a complete case analysis without input of missing values will be performed. If missing data are more than 5%, a blinded statistician will assess whether data are ‘missing completely at random’ based on a rational assessment of the pattern of missing data. If it is concluded that data are not ‘missing completely at random’, multiple imputation using chained equations will be performed by creating at least ten input data sets under the assumption that the data are missing at random. If appropriate, we will also consider carrying out ‘best–worst’ and ‘worst-best’ analyses [32]. We will use outcomes and the most important baseline characteristics in the multiple imputations. The unadjusted, non-imputed analysis will also be made available.

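### Setting the composite to missing when one component is missing discards primary events that are already known, and can bias the relative risk if missingness is related to having an event

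*SAP article*

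**What the plan says.** Outcomes section: "The primary outcome is a composite outcome of VP-shunt implantation, all-cause mortality, or EVD-related infection within 6 months after ictus". This is an any-of-three definition.

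Sample size estimation: "For composite outcomes, one missing component will result in missingness in the composite outcome". No exception is made for a participant in whom another component has been observed. The accompanying safeguard is a reporting one: "Number and percent missing due to a missing component will be stated in the report or in a diagram to avoid biased result, e.g. from", and the sentence ends by giving death alone as its example.

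Handling of missing data: below 5% missing on a primary or secondary outcome, "a complete case analysis without input of missing values will be performed". Above 5%, multiple imputation follows only if a blinded statistician concludes that the data are not missing completely at random. Outcomes and the main baseline characteristics enter the imputation. Best-worst and worst-best analyses are to be considered if appropriate, and the non-imputed analysis is also to be made available.

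**The concern.** With an or-composite, a participant known to have been shunted but with an unknown infection field has had the primary event. So has a participant known to have died with no completed shunt field. The derivation rule gives both a missing primary outcome. Neither the reporting safeguard nor the missing-data section restores them: below 5% they drop out, and above 5% they are either dropped or imputed, with no statement that an observed event must stay an event. Reporting how many were lost does not undo the loss.

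The primary conclusions rest on this outcome. At stake are avoidable loss of information and, if missing components go with having an event, a distorted relative risk. Two statisticians will also code the outcome independently, so a derivation rule at odds with the outcome definition invites a discrepancy between their reports.

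**Working it through.** **Inputs from the SAP article.** Abstract: "event proportion 80% in the gradual weaning group, relative risk reduction 20%, alpha 5%, power 80" (per cent) and "122 participants are required in each intervention group". Sample size estimation: alpha "0.05 (two-sided"). The rates are therefore p1 = 0.80 and p2 = 0.80 × 0.80 = 0.64. All missingness rates below are assumptions.

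**1. The plan's own figure.** Pooled two-proportion formula, mean rate 0.72:

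n = [1.960·√(2·0.72·0.28) + 0.842·√(0.80·0.20 + 0.64·0.36)]² / 0.16² = (1.2445 + 0.5259)² / 0.0256 = 122.4, rounded up to 123.

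The arcsine formula gives 121.3, rounded up to 122. The stated 122 per group is reproduced and is not in dispute. Power at 122 per arm (pooled formula) is 79.9%.

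**2. Missingness related to events.** If a fraction f of event cases lack another component and non-events are complete, the rate among participants with a composite value is p(1−f)/(1−pf).

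| f, both arms | Gradual weaning | Prompt closure | RR | Composite missing overall |
|---|---|---|---|---|
| 0 | 0.800 | 0.640 | 0.800 | 0% |
| 5% | 0.76/0.96 = 0.792 | 0.608/0.968 = 0.628 | 0.793 | (4.0 + 3.2)/2 = 3.6% |
| 10% | 0.72/0.92 = 0.783 | 0.576/0.936 = 0.615 | 0.786 | (8.0 + 6.4)/2 = 7.2% |

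The 5% row lies inside the complete-case zone. The 10% row exceeds the 5% limit, so it describes the non-imputed analysis, or the main one if the data were judged missing completely at random.

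If only one arm loses 10% of its events and there is no true effect (0.80 in both arms), the ratio is 0.80/0.783 = 1.02, or 0.98 with the arms reversed.

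**3. Missingness related to death.** Assume independent components, shunt 63% and infection 5.8% (both in the SAP article), death set to 42.6% so that the composite is 80%, and an effect acting through shunts only.

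- 10% of deaths lack a component (4.3% missing): (0.80 − 0.0426)/0.9574 = 0.791 v (0.64 − 0.0426)/0.9574 = 0.624, RR 0.789.
- 20% of deaths (8.5% missing): 0.781 v 0.606, RR 0.776. Nominal power rises to about 81%, because the effect is exaggerated.

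**4. Missingness unrelated to outcome.** The rates stay at 0.800 v 0.640, RR 0.800, so there is no bias. Power at total composite missingness of 5%, 10% and 20% (115.9, 109.8 and 97.6 per arm) is 77.8%, 75.5% and 70.5%.

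This is not all due to the rule. With 10% of participants lacking a component, keeping known events still leaves about 2 to 5% unresolved in the simulation under the step 3 assumptions. At the planned rates, power is 79.1% with 2% missing and 77.8% with 5%. The part due to the rule is then roughly 79.1 − 75.5 = 3.6 down to 77.8 − 75.5 = 2.3 points.

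**5. Why unresolved participants cannot simply be dropped.** Suppose a fraction m lack a component unrelated to outcome, every event case among them is recovered through another component, and the event-free ones are dropped. The observed rate is p/[p + (1−p)(1−m)].

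- m = 5%: 0.80/0.99 = 0.808 v 0.64/0.982 = 0.652, RR 0.807.
- m = 10%: 0.80/0.98 = 0.816 v 0.64/0.964 = 0.664, RR 0.813.

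That is the upper end. Simulation with partial recovery gives about 0.806 and 0.812. Here the existing rule is unbiased and the half-fix is not.

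**The case against.** The strongest defence is that requiring complete components avoids the selection shown in step 5, where known events are counted while event-free participants with gaps are dropped. The reference to bias from death alone may mean exactly this. The point stands, and it shapes the fix, but it calls for handling the unresolved participants rather than discarding known outcomes.

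It is also fair that the distortions are modest. Even if 12 of 244 participants (4.9%) were missing, all of them events and all in one arm, a null ratio at the 80% rate would move only to 0.80/[(97.6 − 12)/(122 − 12)] = 0.80/0.778 = 1.03.

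A reader might infer four stronger things that the document does not support:

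- **That the rule biases the result in any case.** It does not if missingness is unrelated to outcome. The SAP article gives no rate or pattern, says outcomes are collected after discontinuation, and describes an eCRF strategy to limit gaps.
- **That the whole fall in power in step 4 is the rule's cost.** Part of it remains under any rule, and with death-related missingness nominal power can rise.
- **That the rule is what breaks the statement that "all randomised participants will be included in all analyses".** That tension comes from the complete-case provision and applies to every outcome.
- **That imputation will turn known events into non-events.** Nothing forbids it, but outcomes enter the imputation model, and an observed shunt or death would then predict the composite almost perfectly. It is possible, not shown.

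**Conclusion.** The point holds in a limited form. The derivation rule contradicts the logic of the any-of-three definition and discards participants whose primary outcome is known. The waste of information is certain whenever such a participant exists. Bias is conditional on missing components being related to having an event. In the illustrations with both arms affected, RR moves from 0.80 to between 0.776 and 0.793. Without that relation the cost is precision only, about 2 to 4 points of power if 10% of participants lack a component.

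These sizes rest on assumed missingness rates, on the planning rates of 80% and 64% and, for the death-related and recovery figures, on independent components and an effect through shunts alone. The number of participants with one known event and another component unknown is not given and may be small. This should be fixed; it does not by itself undermine the trial.

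**What to change.** Replace the sentence in Sample size estimation with a derivation rule along these lines:

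- Composite = 1 if any component is known to have occurred within the window, whatever is missing on the others. A known death within the window always gives 1.
- Composite = 0 only if all three components are known not to have occurred.
- Otherwise the composite is unresolved.

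Then add to Handling of missing data, for the primary outcome and whatever the percentage missing: impute the missing components rather than the composite, derive the composite from them, and never overwrite an observed event. Report the best-worst and worst-best bounds for unresolved participants as a fixed item, not only if appropriate. Keep the report of how many participants are unresolved, by arm and by missing component.

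The cost is a few sentences, one line of derivation code and slightly more analysis work. No new data are needed, and the change should be made before the allocation code is broken.

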#### Power estimations

Based on the estimated sample of 244 participants and an unadjusted alpha of 0.05, we used R (R Core Team, Vienna, Austria) to calculate the power for the secondary outcomes:

Previous assessments of SAE in aSAH have not seemed to adhere to ICH-GCP as unlikely low incidences have been reported and seemed defined as probably related to the intervention [16, 17]. Thus, we pragmatically assumed an average of 3 SAEs in the control group with an SD of 1.5, and the minimum clinical difference is pragmatically chosen as 1, which would result in a power of 100% [18]Based on previous assessments, we presume an average of 49.5 [19] in self-assessment of own health of health-related quality of life (EQ-5D-5L) in the control group with an SD of 26.2 [19], and the minimum clinical difference is pragmatically chosen as 11 [20] which would result in a power of 90%Previous reports have assessed the mean FSS score as a continuous outcome. Based on these previous reports, we calculated a power of 100% using an SD of 1.7 and a minimum clinical difference of 1.5 points [12]. Thus, we upgraded the outcome from exploratory to secondary

The exploratory outcome of mRS was initially planned as secondary outcomes given the importance to patients (NCT03948256). As the trial is insufficiently powered to detect the minimal relevant clinical importance for this outcome, we have consequently reclassified it as exploratory outcome [21].

### General analysis principles

Statistical analyses will be handled using the latest stable version of R (R Core Team, Vienna, Austria) and/or Stata (StataCop LLC, Texas, USA). The analyses will be carried out using the intention-to-treat principle where all randomised participants will be included in all analyses. The baseline characteristics will be presented for each group (Tables 2 and 3). The threshold for significance for all outcomes will be below 0.05, as the primary conclusions will be drawn based on the primary outcome [22]. All the remaining secondary and exploratory outcomes will be interpreted as hypothesis generating outcomes.

**Table 2 Tab2:** Baseline characteristics based on simulated data

	A	B
*n*	122	122
Age (mean (SD))	57.8 (0.90)	59.1 (0.50)
Gender, female (*n*, %)	85 (70.9)	90 (73.8)
Hypertension (*n*, %)	46 (37.2)	51 (41.3)
Aneurysm location (*n*, %)		
ICA	19 (15.6)	14 (11.5)
ACA/ACOM	50 (41)	56 (45.9)
MCA	16 (13.2)	11 (9.1)
Basilar artery	25 (20.5)	23 (18.9)
Vertebral artery/PICA	8 (6.3)	10 (8.2)
Pericallosa	4 (3.2)	2 (1.6)
Treatment modality		
Endovascular	50 (41)	56 (45.9)
Surgical	72 (59)	66 (54.1)
WFNS grade		
I	60 (49,2)	55 (45,1)
II	11 (9,0)	12 (9,8)
III	7 (5,7)	12 (9,8)
IV	29 (23,8)	24 (19,7)
V	15 (12,3)	19 (15,6)
Hunt Hess		
1–3	70 (57.4)	74 (60.6)
4–5	52 (42.6)	48 (39.4)
Glasgow Coma Score on admission		
15–14	42 (34.2)	46 (37.7)
13–9	21 (17.1)	17 (14.1)
8–3	58 (47.7)	55 (45.1)
Modified Fisher		
0–3	52 (42.8)	56 (45.9)
4	70 (57.2)	66 (54.1)
Modified LeRoux		
0–5	50 (41)	56 (45.9)
6–16	72 (59)	66 (54.1)
Nicotine use		
Current	21 (17.1)	18 (14.6)
Former	13 (10.4)	10 (8.2)
Never	88 (72.1)	94 (77.1)
Intubated at admission (*n*, %)	45 (36.9)	41 (33.6)
Acute hydrocephalus (*n*, %)	78 (63.9)	71 (59.1)

**Table 3 Tab3:** Summarised results of outcomes based on simulated data

	A	B	Estimate	*p*-value
*n*	122	122		
Primary outcome				
Composite outcome—*n* (%)	43 (35)	36 (30)	*RR (95%CI)* 1.01 (0.99 to 1.03)	0.05
Secondary outcomes				
SAE excl. mortality—median (IQR)	340	320	*median diff (95%CI)* 330 (329 to 349)	0.45
EQ-5D-5L -	60	56	*mean diff (95%CI)* 58 (55.1 to 59.2)	0.69
Fatigue Severity Scale	4.3	4.8	*mean diff (95%CI)* 4.5 (3.9 to 5.3)	0.05
Mean FSS (SD)	5.21 (1.8)	4.1 (1,4)	*mean diff (95%CI)* 4.6 (-4 to 14)	0.69
Clinical fatigue (FSS ≥ 4)	88 (72.3)	82 (67.2)	*mean diff (95%CI)* 3.4 (3.29 to 4.21)	0.34
Components of the primary outcome				
VP-shunt implantation—*n* (%)	40 (33)	32 (26.2)	*mean diff (95%CI)* 34.4 (31.1 to 43.4)	0.03
Mortality—*n* (%)	4 (3.3)	2 (1.6)	*mean diff (95%CI)* 3.4 (-1 to 6)	0.06
Drain-related infection—*n* (%)	9 (7.4)	12 (9.8)	*mean diff (95%CI)* 10.4 (4.3 to 14)	0.05

## Statistical analysis

All analyses will be conducted by two independent statisticians under code, so they will not know the provided intervention group (see statistical reports). The primary analyses will be intention-to-treat analyses.

### Continuous outcomes

Continuous outcomes will be presented as means and 95% confidence intervals for each group, with an annotation in the tables of the percentage of missing data per group. We will use mixed-effects linear regression model adjusted with stratification variables as fixed effect and site as random effects [23].

### Count data outcomes

Count data exploratory clinical outcomes will be presented as medians and interquartile ranges for each group, with an annotation in the tables of the percentage of missing data per group. Count data will be analysed using the van Elteren test from Stata or an equivalent in R [24, 25]. The results will be presented with median differences and Hodges-Lehmann confidence intervals to demonstrate the uncertainty of the results [26].

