### Ordinal outcomes

Ordinal outcomes will be presented as proportions for each level and for simplicity also dichotomized into favourable and unfavourable. For mRS, 0–2 is favourable, and 3–6 is unfavourable [13, 14]; for GOSE, > 5 is favourable, and ≤ 5 is unfavourable [15]. Ordinal outcomes will be analysed using ordinal logistic regression with stratification variables as fixed effect and site as random effects [27, 28]. The results will be presented as relative risks (RRs) and confidence intervals for improving one level on the ordinal outcome [29].

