#### Assessments of underlying statistical assumptions

The chosen analyses have few assumptions, with the main assumptions being related to the linear and logistic regressions [23, 33]. The variables included in the *linear regression models* will be visually assessed for normal distribution using histograms and quantile–quantile plots of the residuals, and for homogeneity using residuals plotted against covariates and fitted values, with the possibility of a logarithmic transformation or applying robust standard errors to minimise deviations from the model.

The deviance divided by the degrees of freedom for *logistic regression model* will be calculated to assess relevant overdispersion. The method used will be mixed effects logistic regression with stratification variables as fixed effect and site as random effects, and if few or zero events are identified, the analyses will instead be carried out using Fisher’s exact test. The robustness of the confidence intervals and *p*-values might be affected by the small sample size, and these will be interpreted with caution. Furthermore, the ordinal logistic regression assumes proportionality of odds across response categories (i.e. the magnitude of improvement or hazard, with a treatment, would be similar irrespective of baseline severity, age, etc.) [27, 29].

If assumptions for ordinal logistic regression are not met, we will use partial proportional odds model if applicable. If this is not possible, we will analyse the data as described for count outcomes.

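### The five EQ-5D-5L dimensions are analysed as counts, so the planned Hodges-Lehmann summary will often read 0, with an interval ending at 0, even where the rank test is significant (minor, exploratory outcomes)

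*SAP article*

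**What the plan says.** Under Outcomes, the exploratory list includes "The remaining dimensions of EQ-5D-5L (mobility, self-care, usual activities, pain/discomfort, and anxiety/depression) at 6 months", tagged "1–5 levels) (count outcome". Table 1 also gives their data type as Count.

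The section Count data outcomes then fixes the analysis. On description: "Count data exploratory clinical outcomes will be presented as medians and interquartile ranges for each group". On testing: "Count data will be analysed using the van Elteren test from Stata or an equivalent in R". On the effect: "The results will be presented with median differences and Hodges-Lehmann confidence intervals to demonstrate the uncertainty of the results". The article states no other effect summary for the dimensions.

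The mRS and GOSE, which are also short ordered scales, are typed as ordinal and handled differently: "Ordinal outcomes will be presented as proportions for each level and for simplicity also dichotomized into favourable and unfavourable". They are analysed by ordinal logistic regression. If proportional odds fails and a partial proportional odds model cannot be used, Assessments of underlying statistical assumptions adds: "If this is not possible, we will analyse the data as described for count outcomes".

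**The concern.** A five-level item is an ordered category, not a count. The Hodges-Lehmann estimate is the median of all between-arm pairwise differences. Here those differences are whole numbers from −4 to 4 with very many zeros, so the estimate can only be a whole or half level, and the interval limits can only be whole levels.

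A treatment can move many patients by one level, and the rank test can detect that, while the median pairwise difference stays at 0. The report would then show a difference of 0 with limits 0 and 0, or 0 and one level, beside p < 0.05. The plan wants the interval to convey uncertainty; an interval of zero width conveys none. Five patient-reported outcomes are affected. Because they are exploratory, their value lies mainly in the size and precision of the effect.

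**Working it through.** **Inputs.** From the article: 122 per arm, two-sided 5% level, five levels, van Elteren test, Hodges-Lehmann interval. The article gives no expected distribution for any dimension, so the level distributions and odds ratios below are assumptions.

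**The plan's own sample size.** With 80% against 0.80 × 0.80 = 64%, the mean proportion is 0.72 and

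n = [1.96·√(2·0.72·0.28) + 0.842·√(0.80·0.20 + 0.64·0.36)]² / 0.16² = (1.245 + 0.526)² / 0.0256 ≈ 122.4.

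The stated 122 is reproduced (123 if rounded up). The plan gives no figure for the Hodges-Lehmann summary itself.

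**Why the summary sticks at 0.** Let D be the control level minus the treated level. There are 122² = 14,884 pairwise differences. The standard order-statistic interval runs from rank k to rank n² − k + 1, with

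k = n²/2 − 1.96·√(n²(2n+1)/12) = 7,442 − 1.96 × 551.25 ≈ 6,361.

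As a fraction, 6,361/14,884 = 0.427; the upper rank, 8,524, is at 0.573. So, when the treated arm does better:

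- the estimate is 0 while the share of pairs with D > 0 is below 0.5 (and likewise for D < 0);
- the interval is 0 to 0 while that share is below about 0.427;
- the lower limit stays at 0 until that share passes about 0.573.

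**Worked example.** Control levels 50/20/15/10/5%, common odds ratio 2. Control cumulative proportions 0.50, 0.70, 0.85, 0.95 have odds 1, 2.333, 5.667, 19. Doubling these gives treated cumulative proportions 0.667, 0.824, 0.919, 0.974.

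- P(D > 0) = 0.20×0.667 + 0.15×0.824 + 0.10×0.919 + 0.05×0.974 = 0.397
- P(D = 0) = 0.50×0.667 + 0.20×0.157 + 0.15×0.095 + 0.10×0.055 + 0.05×0.026 = 0.386
- P(D < 0) = 1 − 0.397 − 0.386 = 0.217

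Since 0.397 is below 0.427, the expected printout is 0 (0 to 0). The probability of a better outcome, counting ties as half, is 0.397 + 0.193 = 0.590, against 0.5 under no effect. The effect is real, and the planned summary does not show it.

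**Simulation.** 2,000 trials per cell, 122 per arm, proportional-odds shift, van Elteren test with four strata. Percentages are among trials with p < 0.05, for odds ratios 1.5 / 2.0 / 2.5.

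| Assumed share at level 1 | Significant (%) | Estimate exactly 0 (%) | Closed interval contains 0 (%) | Interval 0 to 0 (%) |
|---|---|---|---|---|
| 70% | 25 / 63 / 83 | 100 / 100 / 100 | 100 / 100 / 100 | 100 / 100 / 100 |
| 50% | 38 / 79 / 94 | 100 / 99 / 98 | 100 / 100 / 100 | 79 / 71 / 61 |
| 40% | 41 / 81 / 96 | 98 / 89 / 82 | 100 / 99.9 / 99 | 20 / 21 / 15 |
| 30% | 41 / 85 / 98 | 85 / 64 / 40 | 100 / 99 / 95 | 0 / 0.1 / 0.3 |
| 20% (uniform) | 44 / 85 / 98 | 59 / 31 / 11 | 99 / 95 / 79 | 0 / 0 / 0 |

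In every significant trial whose interval contained 0, zero was an endpoint (or both endpoints), never an interior point.

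**The other reading of median difference.** If it means the difference between the two sample medians, it can fall outside its own Hodges-Lehmann interval. With 50% at level 1 this happened in 59 / 35 / 20% of significant trials.

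**The case against.** The strongest reply is that little depends on this. General analysis principles treats every secondary and exploratory outcome as hypothesis generating and rests the main conclusion on the primary outcome. Van Elteren is a valid rank test for ordered categories, so the p-values are sound. The figures above are also conditional on significance and on assumed distributions; with no treatment effect, 0 is the right answer. An interval of 0 to one level still shows direction, and group medians with interquartile ranges are reported too. All of this stands, and it is why the point is minor.

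Fewer than 122 per arm will have EQ-5D-5L data because some participants die or are lost. That changes little. At an assumed 100 per arm, the lower rank fraction is 0.5 − 1.96·√(201/12)/100 = 0.420, so the worked example (0.397) still gives 0 (0 to 0), and the 0.5 threshold for the estimate does not depend on n.

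Three stronger readings are tempting, and the document does not support them.

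- *Discharge GCS has the same fault.* "GCS on discharge from the Neuro Intensive Care Unit and Neurosurgical department" is typed Count only in Table 1, which also types the dichotomous primary composite that way, although Table 3 reports that composite with a relative risk. The full GCS has 13 levels, so any problem would come from clustering near 15. With 55% at 15 within an assumed range of 10–15, the estimate is 0 in practically all significant trials. With scores uniform over 3–15 it is never 0, and the interval contains 0 in 76 / 40 / 15%. The entry criterion of GCS above 9 makes clustering plausible, but it applies at entry, not at discharge.
- *The mRS and GOSE are equally exposed.* They reach the count method only after two ordinal models fail. Their level proportions and favourable/unfavourable split are presented in any case, and the split is also a sensitivity analysis.
- *The estimate is always 0.* It is not: for flat distributions with large effects it is usually non-zero.

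**Conclusion.** The point holds for the five EQ-5D-5L dimensions, as a minor matter of effect reporting. Where 40% or more of patients sit at the best level, the estimate is exactly 0 in about 80–100% of significant trials and the closed interval touches 0 in at least 99%. The share printing 0 (0 to 0) runs from about 15% (40% at level 1) to 100% (70% at level 1). For flatter distributions the estimate is 0 in 11–85% of significant trials, and the interval still touches 0 in 79–100%.

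These figures assume 122 per arm, a proportional-odds shift with odds ratio 1.5 to 2.5, and level distributions the article does not give. Neither the validity of the test nor the primary conclusion is affected. The article gives no reason for handling these ordered items differently from the mRS and GOSE.

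**What to change.** Retype the five dimensions as ordinal in the outcome list and in Table 1, and present proportions per level. Then choose one of two analyses:

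1. Use the ordinal logistic model from Ordinal outcomes (stratification variables fixed, site random) and state that the effect is a common odds ratio with 95% CI. This must be written out, because that section currently describes its results as relative risks for improving one level.
2. Keep van Elteren and replace the Hodges-Lehmann difference with a stratified probability of a better outcome, with CI. The same summary would suit the mRS and GOSE if the fallback is ever used.

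Keep Hodges-Lehmann for length of stay and SAE counts. Extend the change to discharge GCS only if its scores, pooled over arms, cluster heavily at the top of the scale. Make the change before the allocation code is broken.

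The cost is SAP wording and a different model call, with no new data. The downside of option 1 is a proportional-odds check for each dimension, with a stated route if it fails; option 2 can serve as that route.
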